**Figure 2 F2:**
[figure not shown]
Overview data collection methods.

### Intervention

At the start of a care program at the Rotterdam youth care organisation every youth care professional sets, together with the youngster, certain goals to be reached during the care program. These goals can relate to the individual, school, work, family and positive leisure time activities. In the experimental region, specific attention is paid to sport participation as a positive leisure time activity. To increase the attention for sport as a positive leisure time activity, a Care Sport Connector (CSC) is appointed to act as a boundary spanner to connect youth care and sport. As a key-player in the network, the CSC is able to spark initiatives of collaboration between youth care professionals and organised sport clubs, and to identify local sport organisations that are capable of building conducive sport environments. The CSC will bring existing collaborations with local sport clubs to the attention of youth care professionals and will facilitate initiatives of the youth care professionals to make use of sport interventions.

It is expected that a training among the youth care professionals and collaboration with a Care Sport Connector (CSC) in the experimental group will translate to more sport participation among the youngsters of these professionals. The CSC will motivate and train the youth care professionals in the experimental condition to integrate sport activities in the care that they deliver. At the start of every care program, the youth care professional in the experimental regions are expected to inventory, together with the youngsters, the possibilities of sport participation during the care program. The youth care professionals are also expected to be involved in guiding the youngsters to local sport organisations.

Training of the youth care professionals by the CSC will exist of various activities, such as interactive workshops, individual face-to-face sessions, and provision of written (online) information. Various topics will be discussed during these events that are relevant for the youth care professionals, for example focusing on practical barriers that they may encounter when guiding their youngsters to local sport organisations (such as money constraints, ethical issues and lack of parental support). These topics were selected after conducting several interviews with youth care professionals discussing their view of the inclusion of sport in youth care practices. During the intervention, additional events may be organised that match the needs of the youth care professionals and the CSC. As such, the training of the youth care professionals can be seen as coaching-on-the-job and the activities can be adapted to individual needs. All activities that take place will be carefully monitored and recorded, so that in the end a precise description of the actual intervention can be given. The activities of the CSC will continue after the end of this study and will be expanded to other regions of the Rotterdam youth care organisation as well.

Within the experimental regions, specific attention is also paid to the socio-pedagogical climate at the local sport clubs. A pedagogue is employed in the experimental regions to support the local sports clubs in their efforts to create a positive learning environment for all children. Several elements of the socio-pedagogical climate receive specific attention such as the setting and maintenance of basic rules at the sport clubs, improving the pedagogical qualities of the trainers and increasing the involvement of parents at the sport club. Similarly to the activities conducted by the CSC, the activities of the pedagogue are documented during the intervention to be able to provide a clear description at the end of the project.

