**Methods and design:**

This protocol reports on a mixed method study. An intervention that aims to increase the sport participation of socially vulnerable youth, between 12–23 years old, is implemented in three regions of a Rotterdam youth care organisation. The youngsters in the two control regions receive care-as-usual. The main outcome variables, collected via questionnaires, are the life prospect, sense of coherence and self-regulation skills of the youngsters after 6 and 18 months of follow-up. The Motivational Climate Scale is administered to explore the social conditions for a positive effect and interviews are conducted with sport coaches to explore their role in skill development. Interviews with the youngsters are conducted to gain insight on the life experiences that may lead to skill development. The elements of successful partnerships are collected during interviews with youth care professionals, sport coaches and other stakeholders in the sport context.

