## Methods/Design

### Study design

Quantitative and qualitative data for this study will be collected in several phases and for different purposes (see for an overview Figure 2). All the data is gathered in Rotterdam where an intervention is implemented in a youth care organisation that aims to increase the sport participation of socially vulnerable youth. The intervention will be implemented in three regions of the Rotterdam youth care organisation, two regions are in the control group where no intervention activities take place. As randomisation of the regions is not possible, the regions for the experimental and control condition are selected in such a way that the baseline characteristics of the youngsters are as similar as possible (i.e. a non-equivalent control group design). In addition, to avoid contamination, the experimental groups and the control groups are not located in adjacent regions. After describing the intervention into more detail, the data collection methods are discussed per study aim.

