### Study aim 1: effect of sport participation on life prospects

The first study aim focuses on the causal effect of sport participation on the life prospects of socially vulnerable youth and the underlying mechanisms. More specifically, the following hypotheses were formulated:

1. Sport participation during the care program of socially vulnerable youth leads to improved life prospects as measured in: (a.) school level and performance; (b.) work attendance and performance; (c.) subjective health; (d.) well-being, and; (e.) future outlook.

2. Sport participation leads to enhanced self-regulation skills (i.e. planning, self-monitoring, effort and reflection).

3. Sport participation leads to improved SOC-levels.

4. The positive effect of sport participation on life prospects is mediated by self-regulation skills.

5. The positive effect of sport participation, via self-regulation skills, on life prospects is moderated by SOC.

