### Strengths and limitations

There has been a large amount of research investigating the positive outcomes of sport participation. These studies often draw conclusions on the association between sport and the studied outcome based on cross-sectional data. This current study aims to contribute to these findings by investigating the outcomes over a longer period of time (1.5 year) and to report on the causal effects of sport participation by comparing the outcomes of the experimental and the control group. We will explore the life experiences of socially vulnerable youth in the sport context which will allow us to draw a more comprehensive and rich picture of sport-based activities for socially vulnerable youth. In addition, the social conditions and elements of successful partnerships are studied to guide future initiatives of youth care organisations and local sport clubs to use sport as a tool for personal development. The mixed methods design of this study provides insights on the processes occurring in the black box of sport participation that may contribute to the personal development of socially vulnerable youth.

Most studies investigating the factors that influence the performance of the partnership operationalise this performance as the perceived performance by the participants. To explore this relationship for partnerships between youth care organisations and local sport clubs (research aim 4), we use a similar approach. As this part of our study takes place in the same context as the study activities to address research question 1–3, we will also be able to add objective measurements of the partnership’s performance such as the number of youngsters guided to local sport clubs and the presence of beneficial social conditions at local sport clubs.

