This study has several limitations. First of all, the quantitative part of this study has a non-equivalent control group design. The training and support given by the Care Sport Connector (CSC) is organised on a regional level, making randomisation at the individual level of the youngsters impossible. This means that the study may be subject to selection-bias if the youngsters differ on baseline characteristics between the control and the experimental groups. Secondly, due to the voluntary nature of sport participation as part of the treatment plan it is likely that the youngsters who join a sport club differ significantly on certain characteristics from the youngsters that choose not to join. This may distort the effect measurement of sport participation on life prospects, self-regulatory skills and SOC. A third limitation concerns the fact that the intervention is executed on the level of the CSC. The effect of the intervention needs to percolate to the level of the health care professionals and the youngsters, which may reduce the effect of the intervention on the outcome measures. A large sample size is needed to measure changes in life prospects of the youngsters. Fourthly, increasing the sport participation of the youngsters in the experimental groups of the Rotterdam youth care organisation is a big challenge. These youngsters are having difficulties in one or more life domains (e.g. family, school or work) and as such are not necessarily focused on engaging in sports in their leisure time. In order to be able to find significant effects of a small size, we need a large sample. Especially the administration of the third questionnaire, when the youngsters have often left the youth care organisation, will be time-consuming for the researchers. Incentives for completion of all three questionnaires are introduced to increase response rates.

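### The effect of sport is to be drawn from the comparison of experimental and control regions, but no hypothesis tests whether the intervention raised sport participation

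*Protocol article*

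**What the plan says.** The abstract describes "An intervention that aims to increase the sport participation of socially vulnerable youth", and the Study design section gives the same aim. The Intervention section puts the step from intervention to uptake as an expectation: training and the Care Sport Connector "will translate to more sport participation among the youngsters of these professionals".

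The hypotheses begin one step later. Under Study aim 1, hypothesis 1 reads "Sport participation during the care program of socially vulnerable youth leads to improved life prospects", hypothesis 2 "Sport participation leads to enhanced self-regulation skills" and hypothesis 3 "Sport participation leads to improved SOC-levels". Hypotheses 4 and 5 concern mediation and moderation of the sport effect. Hypothesis 6, in the quantitative sub-study of aim 3, concerns its moderation by motivational climate. The main outcomes in the abstract and the primary outcome under Life prospects do not include sport participation.

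Strengths and limitations names the contrast behind the causal claim: the study aims "to report on the causal effects of sport participation by comparing the outcomes of the experimental and the control group". The same section concedes that "increasing the sport participation of the youngsters in the experimental groups of the Rotterdam youth care organisation is a big challenge", and that the effect has to pass through the professionals before it reaches the youngsters and may be weakened on the way.

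Sport participation is measured. Table 1 lists frequency and duration, type of sport, and club membership at T0, T1 and T2, and sport in the treatment plan at T1.

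**The concern.** The argument has two links: the intervention raises sport participation, and sport participation improves life prospects. A comparison of regions tests both links together. If it shows no difference, either link may have failed. The advice to practice differs: find a better way to get these youngsters into sport, or stop expecting sport to improve their prospects.

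The article numbers its hypotheses and names the contrast that carries the causal claim, but the first link is not on the list. For the by-condition comparison, nothing stated requires uptake to be examined before a null is interpreted. The answer the article gives to the expected dilution is a large sample. That helps to detect a small effect but does not show which link failed.

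**Working it through.** **1. Which hypotheses have sport participation as an outcome?**

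| Hypothesis | Cause | Outcome or role |
|---|---|---|
| 1 | sport participation | life prospects |
| 2 | sport participation | self-regulation skills |
| 3 | sport participation | sense of coherence |
| 4 | sport participation | mediation by self-regulation |
| 5 | sport participation | moderation by sense of coherence |
| 6 | sport participation | moderation by motivational climate |

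None of the six. Sport participation is always the cause.

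**2. The plan's own sample size.** Inputs from Sample size: f = 0.20, alpha 5%, power 0.80, three measurements, dropout of 20% and then 30%. A noncentral F calculation with noncentrality N × f² and 2 numerator degrees of freedom gives N = 244, as stated. For dropout, 244 / 0.8 / 0.7 = 435.7, so 436, as stated. Other set-ups also give 244 (for example five groups, between-subject test, correlation 0.7), so the module used cannot be identified. Reading f = 0.20 as a two-group difference of d = 2 × 0.20 = 0.40 SD is therefore an assumption.

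**3. Dilution, as an illustration.** Assume the package acts only through uptake. Then

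between-condition effect = difference in uptake × effect of playing sport.

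With an assumed effect of playing of 0.5 SD:

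- 10 points: 0.10 × 0.5 = 0.05 SD
- 20 points: 0.20 × 0.5 = 0.10 SD
- 30 points: 0.30 × 0.5 = 0.15 SD

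Conversely, for the conditions to differ by 0.40 SD, playing would have to be worth 0.40 / 0.10 = 4.0 SD, 0.40 / 0.20 = 2.0 SD or 0.40 / 0.30 = 1.3 SD.

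If instead 0.40 SD is taken as the effect of playing, the power of the group contrast (equal groups, two-sided 5%, clustering ignored) is:

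| Uptake difference | Group contrast | Power, N = 244 | Power, N = 336 (600 × 0.56) |
|---|---|---|---|
| 100 points | 0.40 SD | 0.88 | 0.96 |
| 50 points | 0.20 SD | 0.35 | 0.45 |
| 30 points | 0.12 SD | 0.15 | 0.20 |
| 20 points | 0.08 SD | 0.09 | 0.11 |

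**4. What a first-stage comparison could show at T1.** With 436 × 0.8, about 348 youngsters (174 per group), the uptake difference detectable with 80% power is about 14.5 to 15 points for control participation of 30% to 50%. With 600 × 0.8 = 480 (240 per group), it is about 12 to 13 points. At 40% participation in both groups, the 95% interval has a half-width of 1.96 × √(2 × 0.4 × 0.6 / 174) = 0.103, or about 10 points; with 240 per group it is 1.96 × √(2 × 0.4 × 0.6 / 240) = 0.088, or about 9 points. Clustering in five regions would widen all of these. A non-significant uptake difference would therefore not show that uptake was unchanged.

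**The case against.** Several objections have force.

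- **The exposure may be actual participation.** Hypotheses 1 to 3 name sport participation, not condition, as the cause. The second limitation worries that youngsters who join a club differ from those who do not, which is a concern about an analysis by actual joining. On that reading a null does not depend on a difference in uptake between regions. This stands and limits the point to the by-condition comparison. The analysis by joining then carries the self-selection that the article concedes.
- **Uptake can be seen.** It is measured three times, the number of youngsters guided to clubs is named as an objective measure under aim 4, and intervention activities are recorded. This also stands: the data exist. What is missing is the prespecified contrast between conditions.
- **The dilution is disclosed.** True, but disclosure does not separate the two explanations of a null.
- **The package has a second target.** A pedagogue works on the climate at clubs in the experimental regions, so the package could change the quality of sport without changing its amount. This weakens the premise of the dilution arithmetic. It is also a further reason not to equate the group contrast with the effect of sport.
- **An article may leave this to the full plan.** A rule for reading a null may well be left there. The numbered hypotheses and the contrast for the causal claim, however, are stated here, and they do not fit together.

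A reader might infer that the authors would report a null as showing that sport has no effect, or that the trial could never tell the two explanations apart. The documents support neither. No section says how a null will be reported, and the collected items allow uptake to be tabulated by condition.

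**Conclusion.** The point holds for the comparison of experimental and control groups. The article draws a causal statement about sport from that comparison, only expects the step that would justify it, doubts that step in its own limitations, and leaves it out of the six hypotheses. A null by condition could be misread as a finding about sport.

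The size is not known, because no uptake figure is given. The 0.05 to 0.15 SD and the power figures rest on assumed uptake differences, an assumed effect of playing, a package that works only through uptake, equal groups, no clustering and, for the power figures and the 0.40 SD target, a two-group reading of f = 0.20. They show the direction and plausible order of the dilution and nothing firmer. The point does not carry over to an analysis by actual participation. The change is worth making because it costs little and alters what a null can support.

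**What to change.** 1. Prespecify a first-stage outcome: the difference between conditions in sport-club membership and in weekly sport time at T1 and T2, adjusted for T0 and allowing for region.
2. Report it with its confidence interval before interpreting hypotheses 1 to 3 by condition.
3. Describe the by-condition contrast as the effect of the intervention package (Care Sport Connector plus pedagogue), not as the effect of sport participation.
4. State the reading in advance: where the interval does not show a clear rise in uptake, a null by condition is uninformative about the effect of sport. Do not conclude from such an interval that uptake was unchanged.
5. Say for each of hypotheses 1 to 3 whether the exposure is condition or actual participation. For the latter, carry over the self-selection caveat.

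The cost is one added outcome, one analysis and a few sentences. The items are already in Table 1 at T0, T1 and T2, so no new data are needed.

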### Study aim 1: effect of sport participation on life prospects

The first study aim focuses on the causal effect of sport participation on the life prospects of socially vulnerable youth and the underlying mechanisms. More specifically, the following hypotheses were formulated:

1. Sport participation during the care program of socially vulnerable youth leads to improved life prospects as measured in: (a.) school level and performance; (b.) work attendance and performance; (c.) subjective health; (d.) well-being, and; (e.) future outlook.

2. Sport participation leads to enhanced self-regulation skills (i.e. planning, self-monitoring, effort and reflection).

3. Sport participation leads to improved SOC-levels.

4. The positive effect of sport participation on life prospects is mediated by self-regulation skills.

5. The positive effect of sport participation, via self-regulation skills, on life prospects is moderated by SOC.

#### Study design and procedure

To test these hypotheses, quantitative data will be collected at three time points during the intervention. Data will be collected at baseline (i.e. when the youngsters enter the care program), after six months follow-up (i.e. at the end of the care program and intervention) and after 18 months follow-up (see Figure 2). The data of the baseline measurement and of the first follow-up will be collected using paper and digital questionnaires administered by the youth care professional. During the second follow-up, a digital and a paper questionnaire will be send to the youngsters who have left the youth care organisation at that point. If necessary, the researchers will go door-to-door to increase the response rate.

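### The T0 and T1 self-reports are administered by the professional who, only in the experimental regions, is trained to promote sport: a risk of differential reporting at 6 months, and a different collection mode at T2

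*Protocol article*

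**What the plan says.** Under Study aim 1, Study design and procedure, data at T0 (entry to care) and T1 "will be collected using paper and digital questionnaires administered by the youth care professional". T1 falls "after six months follow-up (i.e. at the end of the care program and intervention").

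Under Intervention, the Care Sport Connector (CSC) works with one arm's professionals: "The CSC will motivate and train the youth care professionals in the experimental condition to integrate sport activities in the care that they deliver". In the experimental regions these professionals go through the options for sport with the youngster at the start of care, and "The youth care professionals are also expected to be involved in guiding the youngsters to local sport organisations". Under Study design, "two regions are in the control group where no intervention activities take place".

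At T2 (18 months) the procedure changes: "a digital and a paper questionnaire will be send to the youngsters who have left the youth care organisation at that point", and if needed "the researchers will go door-to-door to increase the response rate". Strengths and limitations describes T2 as the time "when the youngsters have often left the youth care organisation".

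According to Measures and Table 1, subjective health, the SDQ, self-regulation, SOC-13, sport participation and expected teacher or employer ratings all come from the youngster's questionnaire. Employment or school status is described as objective.

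**The concern.** In the experimental regions the data collector also delivers the intervention. In the control regions the data collector delivers usual care. Any pressure to please one's own care professional is common to both arms and largely drops out of the comparison. Pressure to report more sport, or more benefit from it, could exist in one arm only, and that part does not drop out.

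The causal claim in Strengths and limitations rests on comparing experimental and control groups, so the exposed contrast is the central one. Sport participation is the hypothesised cause and is reported through the same channel as the outcomes, so errors in exposure and outcome could be correlated. T1 also asks whether sport was part of the treatment plan, which is a question about the professional's own work.

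The collection mode then changes at T2. If a 6-month difference shrinks by 18 months, the data cannot separate a fading effect from a change in how answers were obtained. The stated limitations cover baseline selection, voluntary uptake of sport, dilution through the CSC, and low uptake with follow-up burden. They mention neither the double role nor the change of mode.

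**Working it through.** **Who collects what, by arm and wave**

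| Wave | Experimental regions | Control regions |
|---|---|---|
| T0 | Professional trained to promote sport | Professional giving usual care |
| T1 | Same role, at the end of care and intervention | Professional giving usual care |
| T2, left care | Form sent to the youngster, researcher visit if needed | Same |
| T2, still in care | Not stated | Not stated |

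The mode change between T1 and T2 is the same in both arms. What differs by arm is the stake of the person administering T0 and T1. T0 is at entry to care, and the sport inventory is also at the start of care. The article does not say which comes first.

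**The plan's own sample-size figures**

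Both can be reproduced, although this point does not depend on them. A noncentral F with λ = f²N, f = 0.20, 2 numerator df, α = 0.05 and power 0.80 gives N = 244. The exact G-power option is inferred from this match. For dropout, 244 / (0.8 × 0.7) = 244 / 0.56 = 436.

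**Illustration of size**

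Inputs from the article: 600 expected participants, 20% dropout at time 2, three experimental and two control regions, α = 5%.

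Assumptions: two-sided test, no true effect, youngsters split 3:2 like the regions, and an experimental-arm reporting shift b of 0.10 to 0.20 SD at T1 with none at T0.

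- Respondents at T1: 600 × 0.8 = 480, or 288 v 192.
- SE = √(1/288 + 1/192) = 0.093 SD.
- Rejection probability = Φ(b/SE − 1.96) + Φ(−b/SE − 1.96).

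| b (SD) | b/SE | False-positive rate |
|---|---|---|
| 0.10 | 1.07 | 19% |
| 0.15 | 1.61 | 36% |
| 0.20 | 2.15 | 57% |

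A 1:1 split gives 19% at 0.10 SD and 59% at 0.20 SD. With 436 enrolled (about 349 at T1) the rates are 15% and 45–46%. For two equal groups f = 0.20 corresponds to d = 0.40, so these shifts are a quarter to a half of the effect planned for.

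**Effect of the planned multilevel model**

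Data analysis makes region the third level. Take five regions of 96 respondents and an assumed region ICC of 0.01:

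- Variance of a region mean = 0.01 + 0.99/96 = 0.0203.
- SE = √(0.0203 × (1/3 + 1/2)) = 0.130 SD.

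| b (SD) | Normal reference | t reference, 3 df |
|---|---|---|
| 0.10 | 12% | 9% |
| 0.15 | 21% | 13% |
| 0.20 | 34% | 19% |

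At ICC 0.02 the 0.20 SD row becomes 24% and 15%. A model that accounts for region therefore lowers the rates.

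**Effect of baseline**

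In a change-from-T0 contrast the net shift is b(T1) − b(T0). If the shift is equal at both waves it cancels. If it grows between T0 and T1, while sport is being promoted, only part cancels.

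**The case against.** The strongest reply has four parts.

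- *Administered does not mean observed.* The wording fits simply handing over a form or link. Envelopes and confidentiality rules are fieldwork detail that an article may leave to the full protocol. This stands as far as it goes: the absence of such detail is not the complaint. The stated procedure, with the intervention deliverer as administrator in one arm, is.
- *Goal-setting happens in both arms.* Every professional sets goals with the youngster, covering school, work, family and leisure. Pressure to report better functioning therefore exists in control regions too. This stands and narrows the point. The arm-specific element is attention to sport, so the sport items are the most plausible place for a shift. An effect on the SDQ, SOC-13 or self-regulation is possible but less direct.
- *Not every outcome is self-rated.* Employment or school status is less exposed. This stands.
- *The percentages rest on assumed shifts and an assumed split.* This stands. A reader might take them as lower bounds because clustering is ignored, but the planned region-level model reduces them.

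A reader might also infer that bias is built into the 6-month contrast and gone at T2. The documents support neither. They show an opportunity for differential reporting, not its presence, size or direction. They describe T2 only for youngsters who have left care, which is often but not always the case, and any shift in T0 would carry into a T0-to-T2 change.

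**Conclusion.** The concern holds as a risk. The article assigns T0 and T1 administration to a person who promotes sport in one arm only, nearly all measures are self-reports, and the limitations do not acknowledge this. The 6-month group contrast is therefore open to differential reporting, chiefly on sport participation. At T2 the risk is probably reduced but not shown to be absent, and the change of mode means the 6- and 18-month contrasts are not directly comparable.

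The size cannot be derived from the documents. The 19% to 57% range is an illustration for an unadjusted T1 comparison, conditional on assumed shifts of 0.10 to 0.20 SD and a 3:2 split. With an assumed region ICC of 0.01 the range falls to 12–34% (normal reference) or 9–19% (t on 3 df), and it falls further if the shift is already present at T0. The point is a worthwhile, inexpensive improvement in data collection. It is not evidence that the trial's results would be wrong.

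**What to change.** Change the collection procedure for Study aim 1 as follows.

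1. The professional only hands out the link or paper form. The youngster completes it privately on the existing digital version, or returns the paper form in a sealed envelope addressed to the researchers. The professional does not see the answers.
2. T0 is completed before the sport inventory talk.
3. The same self-completion rule applies at T0, T1 and T2, including for youngsters still in care at T2.
4. Strengths and limitations lists the remaining risk: the professional's double role, and any mode difference left between T1 and T2.

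The cost is envelopes and one instruction to professionals, with no extra staff. The downside is slightly less help for youngsters with reading problems, and possibly a few more missing items.
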